### Preliminary work

The lack of a highly specified model for CRTs [4, 26] led to the development of a fidelity scale by the CORE study team [37]. Fidelity refers to adherence to the standards defining a specific practice; a fidelity scale is a quantitative measure assessing the degree of adherence. The fidelity scale was developed from qualitative interviews with stakeholders [39], a systematic review of previous research [40], and a national survey of CRT managers [26]. The CORE CRT fidelity scale defines 39 fidelity criteria; each item is scored on a scale of 1–5, with 5 indicating excellent fidelity and 1 very low fidelity; and a total score is yielded that ranges from 39–195. The scale has been piloted and used to survey CRT model fidelity across 75 CRT teams in England in 1-day reviews by three trained external reviewers. Whilst completing the 75 team fidelity surveys, researchers collected best practice resources and case study examples that inform the development of the Service Improvement Programme, which is designed to help CRT services achieve high model fidelity and quality improvement.

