## The intervention

The CORE CRT Service Improvement Programme is designed to support teams to identify target areas for service improvement and to produce and implement plans that improve current practice. Structures and resources included in the Service Improvement Programme are available in the online CRT Resource Pack. They include the following:Assessment of adherence to current CRT best practice measured by the CORE CRT fidelity scale. Fidelity reviews will be conducted at baseline and at the end of the 12-month study period with control teams and intervention teams. Intervention teams will receive an additional 6-month review, with feedback from the external reviewers being included on the resulting fidelity report to the CRT manager and team. Intervention teams will be offered a meeting with the reviewers to discuss their 6-month report. This will be used to identify targets for service improvement and planning for how to achieve them and to provide positive reinforcement of any implementation successes achieved during the previous 6 months.Structures to guide service improvement work. A number of structures based on an EBP framework will be utilised to guide service improvement. These structures include a 1-day, whole-team scoping event for each CRT to kick start the Service Improvement Programme and feedback on the fidelity review; service improvement groups (SIGs) of managers and clinical leaders within each CRT meeting regularly to develop service improvement plans (SIPs); and collaboration between CRT managers and staff in teams receiving the intervention, which will be promoted by the research team. Collaboration activities will include an online forum; regular bulletins from the research team about implementation progress at study sites; and at least two meetings/events during the study period to promote sharing of experience, knowledge, and best practice. Evidence suggests that these types of collaborative learning events have the potential to support improvements in the quality of services [42].A local facilitator. Participating NHS Trusts will fund a local facilitator with dedicated time (0.1 full time equivalent for each intervention team) to help teams implement the Service Improvement Programme by encouraging the use of the resource pack; discussion and coaching of the CRT manager; mentoring, supervision, and training of the CRT staff; and liaison with senior Trust management regarding resources or organisational support required to achieve model fidelity. The local facilitator may either be an employee of the participating NHS Trust or an external consultant identified by the study team, depending on local resources and preferences. The facilitator will typically be a manager or senior clinician with experience of working in or with CRTs. Facilitators will be provided with initial and follow-up group training and individual coaching at least once a month by appropriately experienced members of the research study team (a clinical psychologist with CRT clinical experience and a clinical and academic psychologist with expertise in leadership and change management in mental health service contexts). Facilitators will be invited to regular implementation meetings with the study team to offer feedback on how the intervention is progressing and discuss ways of overcoming barriers to service improvement.Access to a web-based resource pack manual, including practical resources, guidance, and training materials to support implementation; case studies from high fidelity CRT services outlining strategies for achieving high fidelity; relevant reading; useful links; video and audio clips of service users, carers, and staff involved in clinical CRT work; and service improvement research providing rationale for fidelity scale items and ideas for improving support. An outline of the structures designed to help facilitate service improvement over the 1-year intervention will also be included.

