
The CORE CRT Service Improvement Programme, with ongoing implementation support from facilitators during the year of the intervention, will thus provide ongoing help to teams during the course of the project in securing leadership support, structuring team workflows to support implementation, and providing expert technical assistance with implementing the CRT model where required, in line with EBP implementation theory [31]. Services in the control group will receive a fidelity review and written report at baseline and at the end of the study period but no other implementation support. Control teams will not be provided with details of the online resource pack; teams within the intervention group will undertake not to share resources or promote service improvement in the control teams until the end of the trial.

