### 2) Service use

We will use routine data to compare service use patterns between teams that have received the Service Improvement Programme and the control teams. Data on admission rate, bed use, and population size will be measured over 6-month periods before and after intervention introduction. We will also explore whether there is any evidence of differences between intervention and control areas in extent of change in rates of compulsory detention under the Mental Health Act and of readmissions within 6 months of an initial admission to acute care. Other routinely collected indicators of CRT functioning, such as referral sources and caseload composition will also be examined. Data will be analysed using Poisson random effects modelling. Either bed use or admission rate will be set as the exposure variable as appropriate.

If differences between the two groups are found, national reference costs will be applied to resource use (admission, bed days and re admissions) to calculate the cost difference between resource kit implementation and control areas. A difference in difference model will be used, looking at before and after effects in the two areas using the most appropriate statistical model as determined by Akaike information criteria (AIC) and Bayesian information criteria (BIC) values. This is likely to be a general linear model with log link and family gamma. The model will take the same form as the Poisson model above.

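### The cost comparison runs only if a service-use difference is found, and it leaves out what the programme costs to deliver

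*Protocol article*

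**What the plan says.** The Analysis section, part 2 (Service use), compares admissions, bed use, compulsory detention and readmissions between the arms without any condition. Conversion to money is different: "If differences between the two groups are found, national reference costs will be applied to resource use (admission, bed days and re admissions". The stated purpose is "to calculate the cost difference between resource kit implementation and control areas". The method is also stated: "A difference in difference model will be used, looking at before and after effects in the two areas", with the model form chosen by AIC and BIC.

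The section called The intervention describes what the intervention teams receive. On staffing: "Participating NHS Trusts will fund a local facilitator with dedicated time (0.1 full time equivalent for each intervention team". On reviews: "Intervention teams will receive an additional 6-month review". On the launch: "a 1-day, whole-team scoping event for each CRT to kick start the Service Improvement Programme". It adds training and at least monthly coaching for facilitators, and at least two shared learning events. For the comparison arm, "Services in the control group will receive a fidelity review and written report at baseline and at the end of the study period but no" further implementation help.

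The Strengths part of the Discussion presents the service-use outcomes as bearing on clinical and cost effectiveness.

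**The concern.** The condition names no outcome, no threshold and no direction. Several service-use outcomes could meet it, and the Background already notes that bed days tend to fall less than admissions, so they may disagree. An estimate reported only after passing a test is biased away from zero. When the test fails, the reader gets no cost estimate and no interval, although the resource-use data are in hand. Cost is a weighted sum of components, so the significance of each component is a poor guide to the size or precision of the total.

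The second matter is what goes into the sum. The costed list covers inpatient use only. Delivery inputs that the same article describes, one of them funded by the participating Trusts, fall in one arm and are not priced. A Trust reading the result as the cost consequence of adopting the programme would be reading a figure that omits the facilitator it would have to fund.

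**Working it through.** **Figure to reproduce.** None. The article gives no number for the cost comparison and no power for service use. Its sample size section concerns the satisfaction questionnaire only, and nothing here rests on it.

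**1. Effect of the condition.** Assumptions, none of them in the article: the trigger is a two-sided test at 0.05, and the triggering estimate Z, in standard-error units, is normal with mean θ and SD 1. Then

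- P(trigger) = Φ(θ − 1.96) + Φ(−θ − 1.96), and
- exaggeration = E(|Z| given |Z| > 1.96) / θ.

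Ignoring the negligible wrong-sign tail, the numerator is [θ·P + φ(1.96 − θ)] / P, where P is the power.

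- At 50% power, θ = 1.96 and φ(0) = 0.399. This gives 1.96 + 0.399/0.50 = 2.76, and 2.76/1.96 = 1.41.
- At 80% power, θ = 2.80 and φ(0.84) = 0.280. This gives 2.80 + 0.280/0.80 = 3.15, and 3.15/2.80 = 1.13.

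Results with both tails included (closed form, agreeing with simulation):

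| Power for the triggering outcome | θ (SE units) | Mean size when triggered ÷ true size |
|---|---|---|
| 20% | 1.12 | 2.26 |
| 30% | 1.44 | 1.81 |
| 50% | 1.96 | 1.41 |
| 80% | 2.80 | 1.13 |

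With no true difference, 5% of trials pass on a single outcome, half in each direction. If any of three outcomes may trigger, the chance is 1 − 0.95³ = 14.3% under independence; the outcomes here are related, so it would be lower.

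These factors describe the estimate that opens the gate. The cost estimate moves with it only as far as the two are correlated. Under joint normality its shift, in its own standard errors, is the correlation times the gate's shift. At 50% power the gate's shift is 2.76 − 1.96 = 0.80 SE, so a correlation of 0.5 would move the cost estimate by 0.40 SE.

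**2. Inputs left out.** The article gives no unit costs, so these are counts only.

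| Input | Intervention arm (15 teams) | Control arm (10 teams) | Costed? |
|---|---|---|---|
| Facilitator | 15 × 0.1 FTE × 1 year = 1.5 FTE-years | 0 | No |
| Six-month review | 15 | 0 | No |
| Whole-team scoping day | 15 | 0 | No |
| Facilitator coaching, learning events | Yes, amount not given | 0 | No |
| Baseline and final review | Each team | Each team | No, but given to both arms |

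The Preliminary work section describes the earlier survey as "1-day reviews by three trained external reviewers". If the trial's reviews take the same form (an assumption), the extra reviews use 15 × 3 × 1 = 45 reviewer-days.

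Every omitted difference is positive and falls in the intervention arm. Net cost difference = calculated difference + delivery cost, with delivery cost above zero, so the calculated difference is always the lower of the two.

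**The case against.** Several points on the other side are sound.

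- **Direction.** A reader might infer that the condition itself favours the programme. It does not. A rise in service use in intervention areas would open the gate just as a fall would. Only the omitted delivery costs tilt the result towards the programme, and even that does not mean a saving will appear.
- **Double counting.** Because admissions, bed days and readmissions appear together, a reader might infer that the same stay will be priced more than once. The text lists types of resource use in a bracket and does not say that each is priced separately and summed. This is a risk to guard against, not a stated plan.
- **Size.** Power and threshold are assumed. At 80% power the exaggeration is modest, and it reaches the cost estimate only in part unless the correlation is perfect. The omitted inputs cannot be put into money from the article.
- **What readers still see.** The service-use comparisons are unconditional, so a failed trigger suppresses the cost estimate, not the underlying results.
- **Scope.** Cost is not among the stated aims or the outcomes in the abstract, health economists are involved in trial management and oversight, and a fuller economic plan may exist.

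The last point does not remove the concern. The article does not leave costing open: it states a trigger, a list of costed items and a name for the result. A fuller plan would have to override that text rather than fill a gap in it.

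**Conclusion.** The concern holds in two parts. The condition makes any reported cost difference a selected one, exaggerated in whichever direction was found, and withholds the estimate otherwise. The illustrative size is 1.13 to 2.26 times for the triggering estimate at 80% to 20% power, assuming a two-sided 0.05 trigger. Separately, and without any such assumption, the calculated difference understates the programme's net cost, because at least 1.5 facilitator FTE-years, 15 six-month reviews, the scoping days and the learning events are left out of the intervention arm.

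The article does not support saying that every reported difference will favour the programme, or that stays will be counted twice. The result affected is secondary; the satisfaction analysis is untouched.

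**What to change.** 1. Delete the condition. Report the difference-in-difference cost estimate with its 95% interval whatever the service-use comparisons show. The resource-use data are already to be collected for both arms and both periods, so this costs only some analysis time.
2. Either add delivery costs to the intervention arm (facilitator time, six-month review, scoping day, coaching and events), or label the result as an acute service-use cost difference that excludes programme cost. Labelling costs nothing. Adding the costs needs a simple log of inputs and hours: the planned monthly monitoring records types and numbers of activities and whether structures such as the scoping day were achieved, but the article does not say that it records hours or costs.
3. State how each item is priced so that each inpatient stay is counted once, and define readmission for this purpose, since the Measures section lists readmissions to acute care separately from hospital admissions. Say also whether days with the CRT, which are collected but absent from the costed list, are included.

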## Discussion

### Strengths

Strengths of the CORE phase 4 study include the following:A multi-site, cluster-randomised trial will provide quality evidence regarding the effectiveness of the CORE CRT Service Improvement Programme. The wide spread of the teams involved will produce generalizable evidence regarding the effectiveness of the programme in a range of contexts. Evidence will be gathered on the relationship between fidelity to a clearly defined model of best practice and service outcomes.The Service Improvement Programme follows a developed US evidence-based practice programme template for achieving high-fidelity implementation of a complex intervention or service model. Process monitoring will confirm whether key elements of the EBP approach are delivered in each team.The mixed methods approach involving measurement of changes in team fidelity, process data, and qualitative evaluation will help to understand trial outcomes, mechanisms of change and barriers and facilitators to implementation and contextual factors that may influence the effectiveness of the trial intervention.The trial outcome measures will allow evaluation of a number of important aspects of CRT services. Service users’ experience of care, measured using the Client Satisfaction Questionnaire [38], is the primary study outcome. The sample size in the trial is sufficient to detect a medium or large difference in satisfaction between participants in the intervention and control arm teams. The experience of care is inherently important in all health services research, and improving the service users’ experience is an overarching goal of the CORE CRT Service Improvement Programme. Service users’ experience of CRT care is especially important to evaluate in our trial, given recent reports of high levels of dissatisfaction with CRT and acute care in the UK [14, 16]. The trial will also investigate the impact of the CORE Service Improvement Programme on other outcomes relevant to the services’ clinical and cost effectiveness, i.e. local admission rates and service users’ recovery following CRT care, and will measure any impact of the team-level intervention on CRT staff well-being.

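### The cost difference is estimated only if an undefined service-use difference is found in the same data that are costed, so it is either selected on its own inputs or missing

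*Protocol article*

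**What the plan says.** Under Analysis, 2) Service use, the article first sets out the service-use comparison: "Data on admission rate, bed use, and population size will be measured over 6-month periods before and after intervention introduction". It adds exploratory comparisons of compulsory detention, readmissions and other routine indicators of team functioning, and names the method: "Data will be analysed using Poisson random effects modelling".

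Costing follows as a conditional step: "If differences between the two groups are found, national reference costs will be applied to resource use". The resources listed are admissions, bed days and readmissions, and the purpose is "to calculate the cost difference between resource kit implementation and control areas". The model is already described: "A difference in difference model will be used, looking at before and after effects in the two areas", with the form chosen by AIC and BIC and a gamma family with log link expected.

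No other section provides a cost analysis that runs regardless of the service-use result. Discussion, Strengths says the trial will investigate "other outcomes relevant to the services’ clinical and cost effectiveness".

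**The concern.** The condition and the estimate share their data. National reference costs act essentially as weights on admissions, bed days and readmissions, so a rule that computes the cost difference only when those counts look different selects the estimate on its own inputs. Two consequences follow:

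- **When the gate opens**, the cost difference has passed a filter that favours large observed differences in either direction, so on average it is further from zero than the truth.
- **When the gate stays shut**, there is no cost difference and no interval. A service-use difference that is not significant is not a zero cost difference: small differences in several components can add up. An interval around a small cost difference is what a commissioner needs to rule a worthwhile saving in or out.

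The trigger is also open. The section does not say which of its several comparisons counts, at what level, or in which direction, so whether a cost result exists is settled after the data are seen. Programme resources are spent in any event: "Participating NHS Trusts will fund a local facilitator with dedicated time (0.1 full time equivalent for each intervention team", as The intervention section puts it.

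**Working it through.** **1. The only power figure in the article.** Sample size gives 97% power for 0.5 SD on the CSQ-8, with 225 and 150 participants, 15 per team and ICC 0.05.
- Design effect = 1 + 14 × 0.05 = 1.70.
- Effective numbers = 225/1.70 = 132.4 and 150/1.70 = 88.2.
- Standard error in SD units = √(1/132.4 + 1/88.2) = 0.137, and 0.5/0.137 = 3.64.
- Power at an assumed 5% level is 95.3% two-sided or 97.7% one-sided, close to the stated figure.

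This concerns satisfaction only. No power is given for any service-use outcome, so gate power below is a range.

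**2. Assumptions that are not in the article.** *Found* means two-sided p<0.05, that is |Z|>1.96. Z is normal with mean λ, where λ gives the stated power. Two gates are considered:
- *Single gate*: one service-use estimate opens it. The cost estimate has the same true standardised effect and correlation 0.5 to 1 with it.
- *Any-of-three gate*: admissions, bed days or readmissions can open it. Power is equal per input, cost is an equally weighted sum, and the common correlation is 0 to 0.9.

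**3. Exaggeration given that the gate opened** (mean reported difference divided by true difference; 2 million simulated draws). Hand check for the single gate at 50% power and correlation 1: λ = 1.96, and the mean of Z above 1.96 is 1.96 + 0.399/0.5 = 2.76, so the ratio is 2.76/1.96 = 1.41.

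| Power per input | Single gate (correlation 0.5 to 1) | Any of three (correlation 0 to 0.9) |
|---|---|---|
| 20% | 1.7 to 2.3 | 1.3 to 2.0 |
| 50% | 1.2 to 1.4 | 1.06 to 1.31 |
| 80% | 1.06 to 1.12 | 1.00 to 1.08 |

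**4. Chance of no cost estimate at 50% power per input.**
- Single gate: 1 − 0.5 = 50%.
- Any of three, independent inputs: 0.5³ = 0.125, about 12%.
- Any of three, correlation 0.9: about 39%.

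**5. No true effect.**
- Single gate: opens in 5% of trials.
- Any of three, independent inputs: 1 − 0.95³ = 14.3%.
- Any of three at correlation 0.5, 0.7 and 0.9: about 12.5%, 11% and 8.4%.

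**6. Coverage of a nominal 95% interval, given that the gate opened.**
- Single gate, correlation 1: about 87% at 20% power, 92% at 30%, 95% at 50% and 97% at 80%.
- Any of three: about 90 to 95% at 20% power and 96 to 97% at 50%.

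**7. Without the condition.** There is always an estimate, and this selection is absent (ratio 1.0).

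**The case against.** The costing is ancillary. Cost is not among the outcomes in the abstract or in the Aims, and the primary result is untouched. The service-use comparisons are run and reported either way, so the resource evidence is not lost, and because the rule is published in advance a missing cost figure would be read as not estimated. All of that stands. It limits the importance of the point but leaves the rule as it is: readers would still lack a modelled cost difference with its uncertainty.

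Several stronger readings are tempting, and the article does not support them:

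- *Any reported saving will be grossly inflated.* The size depends on power that the article does not give, and at 80% power or more the exaggeration is slight. The gate has no direction, so an increase in cost is selected in the same way. A factor near 2.3 is the upper end at 20% power and needs a single gate fully correlated with cost.
- *Half of trials with a real effect would report no cost result.* That holds for a single gate at 50% power. If any of three inputs can open it, the figure is about 12 to 39%.
- *The confidence interval will not have its stated coverage.* Conditional coverage falls materially only at low power, about 30% or less with a single gate. At 50% and above it is at or slightly above nominal.
- *The trial promises a cost-effectiveness result and then withholds it.* The Strengths text reads "clinical and cost effectiveness, i.e. local admission rates" and goes on to recovery after care. It describes service outcomes and commits to no cost estimate.

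**Conclusion.** The concern holds in a limited form. Following the plan as written gives either a cost difference selected on its own inputs or none at all, and the event that decides between the two is undefined. This is a rule that the article states, not a detail left to a fuller document.

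Reading the trigger as two-sided p<0.05, the average exaggeration is about 1.3 to 2.3 times at 20% power, 1.06 to 1.4 at 50% and 1.0 to 1.1 at 80%. At 50% power per input, about 12 to 50% of trials would have no cost estimate. With no true effect, an any-of-three gate would open in 8 to 14% of trials. These ranges rest on the assumed threshold, gate structure and correlations. A looser trigger would change the figures, and the undefined wording adds discretion without removing the selection.

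The loss of the estimate does not depend on how large the exaggeration is. The point merits a change to the plan but does not bear on the primary outcome.

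**What to change.** In Analysis, 2) Service use, delete the opening condition of the costing paragraph. State that national reference costs will be applied to admissions, bed days and readmissions in all cases, that the difference-in-difference cost model already described will be fitted, and that the cost difference will be reported with its 95% confidence interval whatever the service-use results show.

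No trigger then needs defining. The service-use data are collected regardless and the model is already outlined, so no further participants, visits or data are needed. The cost is a wording change and a little more analysis work.

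### The planned between-arm cost difference prices acute service use only and omits the delivery cost that only the intervention arm carries, so it favours the programme by that amount

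*Protocol article*

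**What the plan says.** The costing rule is in the Analysis section under 2) Service use. It is conditional: "If differences between the two groups are found", then "national reference costs will be applied to resource use (admission, bed days and re admissions", with the three items closed off in a parenthesis. The purpose is "to calculate the cost difference between resource kit implementation and control areas". For the model, "A difference in difference model will be used, looking at before and after effects in the two areas", probably in gamma form with a log link.

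The section on the intervention describes what the programme arm receives:

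- "Participating NHS Trusts will fund a local facilitator with dedicated time (0.1 full time equivalent for each intervention team".
- "Intervention teams will receive an additional 6-month review", with feedback and the offer of a meeting with the reviewers.
- "These structures include a 1-day, whole-team scoping event for each CRT", followed by regular service improvement group meetings.
- "Facilitators will be provided with initial and follow-up group training and individual coaching at least once a month".
- An online forum, bulletins and at least two shared learning events.

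The same section gives control teams a fidelity review and report at baseline and at the end, and no further implementation help.

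**The concern.** The result is named as a cost difference between programme and control areas, without qualification. What goes into it is the cost of acute care alone. The resources used to deliver the programme fall in one arm by design, and the first of them is paid for by the Trusts that would read the result. Under Strengths, the article presents local admission rates as relevant to the clinical and cost effectiveness of services, so the figure is likely to be read as bearing on the cost of adopting the programme.

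If the rule is followed as written, a reduction in bed use is set against no outlay. A Trust reading the figure could take an acute-care saving that is smaller than the cost of delivery as a reduction in total cost.

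**Working it through.** **No stated figure to reproduce.** The article gives no cost result and no unit cost. The check is which costs enter the comparison, and then what follows algebraically.

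**Step 1. What is priced and what differs by design.**

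| Item | Intervention (15 teams) | Control (10 teams) | Priced? |
|---|---|---|---|
| Admissions, bed days, readmissions | yes | yes | yes |
| Baseline and 12-month fidelity reviews | yes | yes | no, but the same in both arms, so they cancel |
| Facilitator | 0.1 FTE per team; 15 × 0.1 = 1.5 FTE for the year | none | no |
| 6-month fidelity review | 1 per team; 15 in all | none | no |
| Whole-team scoping day | 1 per team; 15 in all | none | no |
| Facilitator coaching | at least monthly; with 7 facilitators, at least 7 × 12 = 84 sessions | none | no |
| Facilitator group training, improvement groups, learning events | yes | none | no |

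The number of facilitators comes from the section on facilitator monthly updates.

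**Step 2. Direction.** Let S be the mean acute-care cost difference per team, intervention minus control, after the before-and-after adjustment. Let P > 0 be the delivery cost per intervention team.

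- Reported difference = S.
- Difference including delivery = S + P, because delivery cost is zero in the before period and zero in the control arm.
- Reported minus complete = −P, which always favours the programme.
- The sign is wrong whenever −P < S < 0, that is, when there is an acute-care saving smaller than P.

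The difference-in-difference model cannot correct this, because P never enters the data.

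**Step 3. Illustrative size, facilitator time only.** The assumed ranges, none of them from the article, are £40,000 to £80,000 per FTE-year and £300 to £500 per bed day.

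- Cost per team-year: 0.1 × £40,000 = £4,000, up to 0.1 × £80,000 = £8,000.
- Over 15 teams: £60,000 to £120,000.
- Break-even bed days per team: £4,000 / £500 = 8.0, up to £8,000 / £300 = 26.7.

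**Step 4. Time base.** Delivery runs for 12 months. Service use is measured over months 7–12 (Measures, 2. Service use; Procedures). If the whole year of facilitator time is charged to that window, the break-even is 8.0 to 26.7 bed days within the 6 months. If only half is charged (£2,000 to £4,000), it is £2,000 / £500 = 4.0 to £4,000 / £300 = 13.3. The choice changes the answer twofold. The article makes no choice because it does not cost delivery.

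**The case against.** The strongest reply is that the text is open about its scope. The calculation sits under a service-use heading and names the priced items. It uses neither the word saving nor the word net, and promises no economic evaluation of the programme. The article summarises a fuller protocol, and health economists sit on both the management group and the steering committee, so delivery may be costed elsewhere. This has some force, but the article does not defer the matter: it lists what is priced and gives the result an unqualified name. That is a stated rule with an error in one direction, not detail lost in condensing.

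Four stronger readings are tempting, and the article does not support them:

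- *The plan intends to claim a saving.* It says no such thing. A misleading sign is a possible consequence, not a stated aim.
- *A programme with no effect would look cost-neutral.* Costs are calculated only if the groups differ. If they do not, no cost result appears, and the delivery cost goes unreported rather than being shown as zero.
- *A particular number of bed days is needed to break even.* Only the 0.1 FTE is a trial figure in that sum. The prices are assumed. Adding staff time for the scoping day, group meetings and the extra review would need further assumptions about attendance and hours.
- *Existing records already allow full costing.* The monthly facilitator interviews and process data cover the activities, their type and whether structures were achieved. Nothing says that hours, attendance or grade are recorded.

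It is also fair to say that this is a conditional, secondary calculation. It touches neither the primary outcome nor any hypothesis test.

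**Conclusion.** The point holds in a limited form. As written, the between-arm cost difference leaves out every input that exists only in the intervention arm, and so favours the programme by exactly its delivery cost per team. The direction follows from the design and needs no assumption. The amount cannot be derived from the article. Facilitator time is fixed at 0.1 FTE per team, and its illustrative equivalent of 8 to 27 bed days per team rests wholly on assumed salary and bed-day prices and on charging a full year of delivery. The other inputs would raise it by an unknown amount. The clinical effect estimates are unaffected. What changes is what the cost result can support: the price of a change in acute care, but not the cost of having the programme.

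**What to change.** In Analysis, 2) Service use, rename the result and add a second one. Suggested wording:

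*The difference in acute service-use cost, excluding programme delivery cost, will be estimated as described. A net difference will be reported beside it, adding the cost of the facilitator (0.1 FTE per intervention team) and of the other scheduled intervention-only inputs: the 6-month review, scoping day, facilitator training and coaching, and learning events. Quantities will be taken from the design, with stated assumptions and a range where hours were not recorded.*

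Three details should be settled in the same place:

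- **Whose costs count.** Trusts fund the facilitator, while the coaching is given by members of the research team, who also promote the collaboration activities.
- **Time base.** State how 12 months of delivery is set against the 6-month service-use window, and show the result under the alternative.
- **Scale.** Delivery cost is a fixed sum per team, so it should be added on the money scale and not to a log-link coefficient.

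The cost is a modest amount of extra work. The facilitator component needs only a unit price. The other components need assumptions, because the intervention was already under way when the article was submitted. The net figure will be less favourable to the programme than the acute-care figure alone. If the net analysis is not wanted, the relabelling alone still removes the misleading name.
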